## Abstract

**Background:**

Continuous glucose monitoring (CGM) is increasingly being recognized as the new standard of care for glycemic monitoring in people with type 2 diabetes (T2D). However, despite advances in therapeutics and technology, glycemic control remains suboptimal. Team-based approaches involving pharmacists, particularly in primary care, have shown to be effective in addressing these shortcomings yet have not been rigorously evaluated in the literature.

**Objective:**

Herein we present the protocol for a study that seeks to evaluate the change in hemoglobin A_1c_ (HbA_1c_) in people with T2D using CGM under a pharmacist-led approach as compared with a pharmacist-led approach using no CGM (only self-monitoring blood glucose with a glucometer). We will also assess changes in CGM-derived glycemic outcomes, health behavior, and safety outcomes among the pharmacist-led CGM cohort.

**Methods:**

This is a 12-week prospective cohort study in an academic family medicine department. We will enroll adults with T2D and a HbA_1c_ level of ≥8%. Participants in the intervention cohort will wear a CGM sensor (FreeStyle Libre 2) for 12 weeks and receive structured diabetes self-management education and support from a pharmacist. Each participant in the intervention group will have 5 visits with a pharmacist. The primary objective is the between-group difference in change in HbA_1c_ levels from baseline to 12 weeks between the intervention and historical cohort. Secondary objectives include a change in CGM-derived metrics among the intervention group from baseline to 12 weeks, and a change in health behavior via the Summary of Diabetes Self-Care Activities measure from baseline to 12 weeks in the intervention cohort. A CGM survey will also be administered to participants in the intervention cohort to evaluate changes in diet, physical activity, general lifestyle, and medication adherence. Safety endpoints will also be evaluated. The primary and secondary outcomes will be analyzed within and between groups using descriptive statistics, with a multivariable regression analysis conducted as appropriate to adjust for potential known confounding effects.

**Results:**

This study was funded in July 2023. We began enrolling participants in December 2024. At the time of writing, 3 participants have been enrolled. It is anticipated that we will conclude this study in December 2025 and expect to disseminate results in March 2026.

**Conclusions:**

Results of this study will further elucidate the role of pharmacist-led CGM in primary care.

**Trial Registration:**

ClinicalTrials.gov NCT06572306; https://clinicaltrials.gov/study/NCT06572306

**International Registered Report Identifier (IRRID):**

PRR1-10.2196/67014

## Introduction

More than 38 million adults in the United States have diabetes, with the prevalence estimated to triple by 2060 [1]. The majority of those with diabetes have type 2 diabetes (T2D) [1]. Frequent patient self-monitoring of blood glucose (SMBG) in conjunction with hemoglobin A_1c_ (HbA_1c_) testing is often required in people living with T2D [2]. HbA_1c_ and SMBG have long been recognized as the standard of care for assessment of glycemic control [3]. However, limitations to these metrics exist. HbA_1c_ is an average of glycemia over 2-3 months, with variability in the average glucose range at any HbA_1c_ level [4]. People with similar HbA_1c_ levels can have vastly divergent glycemic patterns [4]. Limitations also extend to SMBG, as it only provides glucose data at one point in time, thereby missing time spent in the normal glycemic range, and potential identification of hyperglycemia or hypoglycemia [4].

Continuous glucose monitoring (CGM) provides glycemic metrics beyond HbA_1c_ and SMBG [5]. CGM is increasingly being recognized as the new standard of care for glycemic monitoring in people with T2D [6-8]. CGM-derived glycemic metrics provide more actionable data for patients and clinicians versus HbA_1c_ and SMBG. Importantly, CGM has also been shown to improve patient engagement and positive health behavior change, improve glycemic control, and reduce hypoglycemia in people with T2D [9-11].

Despite advances in therapeutics and technology, glycemic control remains suboptimal with 50% of patients unable to reach glycemic goals [12]. Failure to reach these goals increases the risk of microvascular and macrovascular diabetes complications [13]. While the reasons for failure to reach glycemic control are multifactorial, clinical inertia has been shown to be associated with an inability to achieve glycemic control [14]. In addition, patient inertia may result from lower self-efficacy and a lack of effective tools to make behavior change, further driving this issue [14,15].

Our recent work suggests that pharmacist-led interventions in close collaboration with medical providers in primary care settings may overcome diabetes-related inertia [16-18]. The trend in team-based care involving a pharmacist is widely recognized at the national and international level and is now the standard of care in a number of medical centers [19]. Several small retrospective studies have found improvements in glycemic control with a pharmacist-led CGM clinical service [20]. However, in our recent scoping review, we identified only 1 published prospective study evaluating a pharmacist-led CGM service [20]. The aim of this work is to further elucidate the impact of pharmacist-led CGM on glycemic control and change in health behavior in people with T2D.

## Methods

### Study Objectives

The primary objective of this study is to determine the impact of pharmacist-led CGM on glycemic control in people with T2D. The secondary objectives are to assess change in CGM-derived glycemic outcomes, change in health behavior, and safety outcomes.

### Practice Setting

This study will take place in the University of South Florida (USF) Health Department of Family Medicine, where people with T2D are routinely managed by pharmacists for chronic disease state management in collaboration with their primary care physician. Routine care consists of appointments that involve reviewing a patient’s blood glucose log or CGM sensor readings, ordering laboratory tests, and adjusting or initiating medication therapy under supervision and in collaboration with medical providers. The study procedures will be incorporated into the patient’s routine appointments. No change in the patient’s routine medical care will occur with their primary care provider or other medical specialists as a result of participating in this study.

### Study Design

This is a 12-week prospective cohort study. Inclusion and exclusion criteria are shown in Textbox 1. Enrolled participants in the intervention group will wear a CGM sensor (Abbott FreeStyle Libre 2; n=20) and receive structured diabetes self-management education and support (DSMES) from a pharmacist in a family medicine clinic. Each participant in the intervention group will have 5 visits with a pharmacist. DSMES will be provided in line with the 2022 National Standards for DSMES [21].

A historical cohort will be used to compare outcomes against the intervention group for the primary outcome. The historical cohort will include participants with T2D and a HbA_1c_ level of ≥8% seen by a pharmacist practicing under a similar scope of practice in a different outpatient clinic within the same health system between January 1, 2020, and January 7, 2024. Participants in this cohort (n=20) will have only used SMBG, and not used CGM within 6 months of the index date (defined as the first visit with a pharmacist during the study time frame). Reporting of research for this cohort study will follow the STROBE (Strengthening the Reporting of Observational studies in Epidemiology) checklist (Multimedia Appendix 1).

Inclusion and exclusion criteria.
**Inclusion criteria**
Type 2 diabetes.Hemoglobin A_1c_ level of ≥8%.Compatible smartphone with FreeStyle Libre 2 continuous glucose monitoring system.Current use and access to a glucometer for self-monitoring of blood glucose.
**Exclusion criteria**
Any continuous glucose monitor use within 6 months before study enrollment.Pregnant and planning to become pregnant during the study time frame.History of hypoglycemia requiring third-party assistance.History of diabetic ketoacidosis or hyperosmolar hyperglycemic state within 6 months before study enrollment.Known allergy to medical-grade adhesives.Current use of systemic steroids for any medical condition.Current use of dialysis.

### Recruitment

Recruitment began in December 2024, with an expected study completion date of December 2025. Participants included in the intervention group will be recruited from the USF Health Department of Family Medicine. Screening and enrollment will be performed by the pharmacist on the basis of routine care. Participants already scheduled for a visit with a pharmacist for diabetes care and education will be screened for eligibility by review of the medical record. Informed consent will be completed at the first visit.

### Sample Size

The sample size (n=40) was determined on the basis of available research funding, balancing statistical power with financial constraints. While a larger sample could enhance the external validity of findings, budgetary limitations necessitated an approach that maximized efficiency while maintaining sufficient power to detect meaningful effects. This sample size aligns with previous studies of similar scope and ensures the study remains methodologically rigorous within resource constraints [16-18,20].

### Study Visits

An overview of activities that will take place at each study visit for participants enrolled in the intervention cohort is shown in Table 1.

**Table 1 table1:** Study activities.

Study activity	Visit 1 (baseline)	Visit 2 (week 2)	Visit 3 (week 4)	Visit 4 (week 6)	Visit 5 (week 12)
Review eligibility	✓				
Obtain informed consent	✓				
Collect patient baseline characteristics	✓				
Collect vital signs (blood pressure, weight, pulse, and oxygen saturation)	✓	✓	✓	✓	✓
Review and collect medications	✓	✓	✓	✓	✓
Assess diet and fitness activity at baseline	✓				
HbA_1c_^a^ blood sample	✓				✓
FSL2^b^ CGM^c^ sensor placement and education	✓				
Provide 5 FSL2 CGM sensors to participants		✓			
Review ambulatory glucose profile and upload into electronic health record		✓	✓	✓	✓
Administer structured diabetes self-management education and support	✓	✓	✓	✓	✓
Provide food and fitness logs	✓				
Assess and collect food and fitness logs		✓	✓	✓	✓
Administer CGM survey		✓	✓	✓	✓
Administer summary of diabetes self-care activities measure	✓				✓
Assess CGM-related adverse events		✓	✓	✓	✓
Provide after-visit summary to participants	✓	✓	✓	✓	✓

^a^HbA_1c_: hemoglobin A_1c_.

^b^FSL2: FreeStyle Libre 2.

^c^CGM: continuous glucose monitoring.

### Outcomes and Covariates

#### Glycemic Control

To evaluate the primary objective the between-group difference in change in HbA_1c_ levels from baseline to 12 weeks will be compared between the intervention and historical cohort.

#### CGM-Derived Metrics

For the secondary objective, the CGM-derived metrics shown in Textbox 2 will be compared within the intervention group from baseline to 12 weeks.

Continuous glucose monitoring–derived glycemic metrics.Change in time in range (TIR) at 12 weeks (%).Change in mean sensor glucose concentration at 12 weeks (mg/dL).Change in time below range at 12 weeks (%).Change in time above range at 12 weeks (%).Change in glycemic variability (SD and coefficient of variance) at 12 weeks.Change in the number of participants increasing by 5% or more in TIR at 12 weeks.Change in the number of participants increasing by 10% or more in TIR at 12 weeks.Change in the number of participants achieving >70% TIR at 12 weeks.Change in the number of participants achieving hemoglobin A_1c_ <7% at 12 weeks.Change in the number of participants achieving hemoglobin A_1c_ <8% at 12 weeks.

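### Four of the five responder counts in Textbox 2 have no usable baseline for the stated within-group comparison; the two HbA1c thresholds belong in a comparison with the historical cohort

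*Protocol article*

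**What the plan says.** The CGM-Derived Metrics section of the protocol article states that the items in Textbox 2 "will be compared within the intervention group from baseline to 12 weeks". Five of those items are responder counts:

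- "Change in the number of participants increasing by 5% or more in TIR at 12 weeks"
- "Change in the number of participants increasing by 10% or more in TIR at 12 weeks"
- "Change in the number of participants achieving >70% TIR at 12 weeks"
- "Change in the number of participants achieving hemoglobin A_1c_ <7% at 12 weeks"
- "Change in the number of participants achieving hemoglobin A_1c_ <8% at 12 weeks"

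The inclusion criteria in Textbox 1 require "Hemoglobin A_1c_ level of ≥8" per cent. Study Design applies the same threshold to the comparator: "The historical cohort will include participants with T2D and a HbA_1c_ level of ≥8% seen by a pharmacist". That section assigns the historical cohort to the primary outcome. Statistical Analyses says that primary and secondary outcomes are analysed both within and between groups with descriptive statistics. It names no test for the responder counts.

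**The concern.** A change in a count needs a count at both ends. For the two HbA1c thresholds the starting count is fixed at or near zero by the entry rule. For the two TIR gains there is no starting count, because each item is itself a change from baseline. The figure reported as a change is then, in effect, the week-12 count under another name.

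The wording invites the reader to take any HbA1c crossing as improvement due to the intervention. The study's stated objective is to compare pharmacist-led care with CGM against pharmacist-led care without it. A within-group count in patients selected for a high HbA1c mixes three things: CGM, the pharmacist's care, and regression to the mean. The historical cohort is selected by the same HbA1c rule, also receives pharmacist care, and already supplies HbA1c for the primary outcome. The section that defines these items nevertheless prescribes the comparison that cannot answer the question.

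**Working it through.** **Inputs from the protocol article.** 20 participants per cohort (Study Design); HbA1c at least 8% in both cohorts (Textbox 1, Study Design); within-group comparison of the Textbox 2 items (CGM-Derived Metrics). The stated total of 40 agrees with 20 + 20. It was set by funding, and no alpha, SD, effect size or responder rate is given, so there is no planned figure for these items to reproduce.

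**Step 1: baseline count for each item.**

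| Item | Baseline count | Reason |
|---|---|---|
| HbA1c <7% | 0 or near 0 of 20 | excluded by eligibility |
| HbA1c <8% | 0 or near 0 of 20 | excluded by eligibility |
| TIR gain ≥5% | none (0 by definition) | the item is a change from baseline |
| TIR gain ≥10% | none (0 by definition) | the item is a change from baseline |
| TIR >70% | free to take any value | no TIR entry criterion |

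The HbA1c entries read near zero because Recruitment screens eligibility from the medical record, while Table 1 takes a new HbA1c sample at Visit 1. A few Visit 1 values may fall below 8%.

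**Step 2: what a test would do, if one were applied.** With nobody able to move from responder to non-responder, all discordant pairs lie on one side, and the two-sided exact McNemar p-value for k crossings is 2 × 0.5^k.

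- k = 5: 2 × 0.5^5 = 0.0625
- k = 6: 2 × 0.5^6 = 0.031

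So 6 of 20 would reach a two-sided 0.05 level (assumed here), whatever caused the crossings.

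**Step 3: how often 6 of 20 would fall below 8% with no treatment effect.** The article gives no HbA1c mean, SD or correlation, so these are assumptions. Let p be the probability that follow-up HbA1c is below 8% given a qualifying value of at least 8%, with the qualifying value taken as baseline and the two values bivariate normal. The chance of interest is P(X ≥ 6) with X binomial(20, p).

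| Assumptions | p for <8% | P(X ≥ 6) |
|---|---|---|
| mean 7.5, SD 1.5, correlation 0.6 | 0.377 | 0.83 |
| mean 8.0, SD 1.5, correlation 0.8 | 0.204 | 0.21 |
| mean 8.0, SD 1.5, correlation 0.9 | 0.14 | 0.056 |
| mean 8.5, SD 1.5, correlation 0.9 | not shown | 0.016 |
| mean 7.5, true SD 1.5, within-person SD 0.8 | 0.269 | 0.46 |
| mean 8.5, true SD 1.5, within-person SD 0.3 | 0.067 | 0.002 |

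The two ways of setting the noise are linked. With total SD 1.5, correlations of 0.6 and 0.8 imply within-person SDs of 1.5 × √0.4 = 0.95 and 1.5 × √0.2 = 0.67. With true SD 1.5, within-person SDs of 0.8 and 0.3 imply correlations of 2.25/(2.25 + 0.64) = 0.78 and 2.25/(2.25 + 0.09) = 0.96. The range is therefore mainly a statement about how repeatable HbA1c is in these patients.

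For <7%, the chance of at least 6 of 20 stays below 5% throughout.

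**Step 4: the two comparisons side by side.** Suppose both cohorts have the same true week-12 proportion below 8%, so CGM adds nothing.

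| Common true proportion | Within-group test against zero rejects | Fisher's exact test between cohorts rejects |
|---|---|---|
| 30% | 58% | 2.5% |
| 40% | 87% | 2.4% |
| 50% | 98% | 2.0% |

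**Step 5: precision of the between-cohort comparison.** For 30% versus 50%, the standard error of the difference is √(0.3 × 0.7/20 + 0.5 × 0.5/20) = √0.023 = 0.152, so a 95% interval is about ±30 percentage points (1.96 × 0.152 = 0.297). Fisher power is 16% for 30% versus 50%, 35% for 30% versus 60%, 60% for 30% versus 70%, and 85% for 30% versus 80%.

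**The case against.** The strongest reply is that no test is planned. CGM-Derived Metrics says only that the items are compared, and Statistical Analyses speaks of descriptive statistics. A reader might infer that the plan has a false-positive rate of some stated size. The article does not support that: the McNemar figures belong to a test it does not name, under inputs it does not give. This stands, and Steps 2 to 4 are illustrations only. A descriptive change from zero still has the same defect, because it cannot fall and has no comparator.

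A reader might also infer that the between-cohort comparison is ruled out. It is not plainly so. Study Design ties the historical cohort to the primary outcome and CGM-Derived Metrics prescribes a within-group comparison, but Statistical Analyses mentions between-group analysis of secondary outcomes. This is a conflict to resolve, not a settled exclusion.

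Third, it would be too strong to say that all responder items are affected, or that the HbA1c counts can only improve. TIR >70% can be met or lost, and a few Visit 1 HbA1c values may already be below 8%.

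Fourth, the TIR gain items can be read as a drafting slip for week-12 responder counts. That is probably what is meant, and dropping the reference to a change cures it.

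Finally, the continuous HbA1c contrast is already the primary outcome, and a dichotomised version at 20 versus 20 has little power. This too stands, and it limits how the result should be presented. It does not make the within-group version informative.

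**Conclusion.** The point holds for four of the five responder items. For HbA1c <7% and <8% it follows from the entry criterion and the stated comparison; the one assumption is that the qualifying value is close to the baseline value. For the TIR gains it follows from their definition.

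The numerical consequence depends on assumptions. If HbA1c <8% were tested against a zero baseline, the chance of a nominally significant result with no treatment effect would lie between under 1% and about 80%, according to the HbA1c mean, SD and correlation assumed. For <7% it is small. What does not depend on those inputs is that the HbA1c count starts at or near its floor and that its rise cannot be attributed to CGM.

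These are secondary outcomes and the primary analysis is unaffected. The correction should be made, but it does not threaten the study.

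**What to change.** Reword Textbox 2 and reconcile it with Study Design and Statistical Analyses:

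1. **HbA1c <7% and <8%:** move them out of the within-group CGM metrics. Report the week-12 proportion in each cohort with a between-cohort risk difference and confidence interval, adjusted for baseline HbA1c where the counts allow.
2. **TIR gain ≥5% and ≥10%:** report the proportion reaching each gain at week 12 with an exact confidence interval and no comparison with baseline.
3. **TIR >70%:** keep the within-group comparison.
4. **Use of the historical cohort:** state in one place which secondary outcomes are compared between cohorts, so that the three sections agree.

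The cost is rewording. The HbA1c values are already needed for the primary outcome, and the article reports only 3 participants enrolled at the time of writing. The drawback is that a 20 versus 20 difference will be imprecise and remains confounded by the non-randomised, historical comparison. It should be presented as an estimate with its interval, not as a confirmatory test.

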#### Summary of Diabetes Self-Care Activities

To evaluate change in health behavior we will administer the Summary of Diabetes Self-Care Activities Measure (SDSCA) at baseline and week 12 in the intervention cohort. The within-group difference from baseline to week 12 will be assessed. The SDSCA is a valid and reliable measure of diabetes self-management, which assesses diet, exercise, blood-glucose testing, foot care, and smoking [22]. The strength of the SDSCA includes its brevity and ease of scoring. The SDSCA is a survey scored on an 8-point Likert scale (0-7). Higher scores indicate better compliance with diabetes self-care, whereas a lower score indicates poor self-care performance [22].

#### CGM Survey

We will administer a CGM survey (Table 2) at each visit following the first visit in the intervention cohort. The within-group difference in responses from baseline (second visit) to the end of the study among the intervention group will be evaluated.

**Table 2 table2:** Continuous glucose monitoring survey.

Domain and questions		Response	

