**Dietary habits**			
	Have you noticed how different foods affect your glucose levels since using CGM^a^?	Yes No Not sure	
	Have you changed your consumption of sugared beverages since using CGM?	Yes, I have reduced or avoided them No, my consumption is the same I did not consume them before CGM use	
	Have you changed your consumption of high-carbohydrate foods (eg, rice and cereals) since using CGM?	Yes, I have reduced them Yes, I have avoided them No, my consumption is the same I did not consume them before CGM use	
	Do you read nutrition labels more frequently since using CGM?	Yes No I already did this before CGM use	

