## Discussion

### Principal Findings

To our knowledge, this will be the first study to prospectively analyze the impact of a pharmacist-led CGM intervention on glycemia and health behavior in people with T2D in a primary care setting. Our study is unique in that it is not only designed to assess the glycemic benefits of CGM in people with T2D in primary care but also aims to elucidate behavior change resulting from CGM use under a pharmacist-led approach.

We hypothesize that the mean change in HbA_1c_ will be greater for participants enrolled in the intervention cohort as compared to the historical control cohort at 12 weeks. We also hypothesize that participants enrolled in the intervention cohort will experience an improvement in CGM-derived metrics (time in range, mean glucose, time below range, time above range, and glycemic variability) at 12 weeks. For health behavior, we hypothesize that the mean SDSCA score will be higher at 12 weeks compared with baseline. Finally, we hypothesize that an improvement in diet, physical activity, general lifestyle, and medication adherence will be observed on the CGM survey from baseline (second visit) to the end of the study among the intervention group.

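### The CGM survey is compared from Visit 2 to study end, but several items already ask about change since CGM, so change made in the first two weeks counts as none

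*Protocol article*

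**What the plan says.** **Survey timing.** The CGM Survey section says "We will administer a CGM survey (Table 2) at each visit following the first visit in the intervention cohort", and then "The within-group difference in responses from baseline (second visit) to the end of the study among the intervention group will be evaluated". The hypothesis under Principal Findings uses the same reference point: "improvement in diet, physical activity, general lifestyle, and medication adherence will be observed on the CGM survey from baseline (second visit".

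**Start of the intervention.** Table 1 (Study Visits) labels Visit 1 as baseline. It puts "sensor placement and education" there, and the activity "Administer structured diabetes self-management education and support" is ticked at Visit 1 and every later visit. Visit 2 is at week 2.

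**Survey wording.** Table 2 has ten closed items. A typical one is "Have you changed your consumption of sugared beverages since using CGM".

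**Sensor metrics.** The CGM-Derived Metrics section says these "will be compared within the intervention group from baseline to 12 weeks". It defines no baseline window. The activity "Review ambulatory glucose profile and upload into electronic health record" is first ticked at Visit 2.

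**The concern.** An item that asks whether something has changed since CGM began already gives a change from before CGM. Comparing its Visit 2 and Visit 5 answers takes a difference of two change reports. What remains is change that first appeared after week 2. The more quickly participants respond, the smaller the contrast becomes.

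Several of these items also let participants say that they already had the good habit, or never had the poor one, before CGM. Such an answer describes life before CGM and is neither better nor worse than Yes or No, so a difference in responses has no clear meaning for it.

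The stated hypothesis about diet, physical activity and lifestyle is read from this contrast. Future Directions says the data are meant to support funding for a larger randomized trial, so understated behaviour change would carry over into that planning.

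**Working it through.** The article gives no effect size, SD or test for the survey, so there is no figure to reproduce. The check sets the schedule beside the wording and then illustrates the size.

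**1. Timing.** CGM and education start at week 0 (Visit 1). The first survey is at week 2 (Visit 2) and the last at week 12 (Visit 5). No survey answer predates the intervention.

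**2. Items in Table 2.**

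| Closed item | What the answer records | Option referring to habits before CGM |
|---|---|---|
| Sugared beverages | Change since CGM | Yes |
| High-carbohydrate foods | Change since CGM (reduced and avoided are separate) | Yes |
| Nutrition labels | Change since CGM | Yes |
| Physical activity | Change since CGM | Yes |
| Noticing food effects | Arguably change (awareness) | No |
| Healthier lifestyle | Arguably change | No |
| Activity on a glucose rise | Level | No |
| Scan frequency | Level | No |
| Motivation | Level | No |
| Medication-taking | Level | Yes |

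Four items are clearly change items, two arguably so, and four are level-type.

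**3. Size for a change item.** Assumptions: all 20 intervention participants answer and are able to change; 12 report the change at week 12; a fraction f of those 12 had already changed by week 2; nobody reverts.

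- Yes at week 12 = 12/20 = 60%.
- Yes at week 2 = 12f/20.
- Planned contrast = 12(1 − f)/20.
- The discordant pairs, d = 12(1 − f), all go one way, so the two-sided exact McNemar p is 2 × 0.5^d, capped at 1. The article names no test; this one is used only for illustration.

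| f | Yes at week 2 | Planned contrast | Report the change at week 12 | p |
|---|---|---|---|---|
| 0 | 0% | 60 points | 60% | 0.0005 |
| 0.25 | 15% | 45 points | 60% | 0.004 |
| 0.50 | 30% | 30 points | 60% | 0.031 |
| 0.75 | 45% | 15 points | 60% | 0.25 |
| 1 | 60% | 0 points | 60% | 1.0 |

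The same week-12 result gives a contrast anywhere from 60 points to 0, depending only on when people changed.

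**4. Sensor metrics (inferred).** CGM use in the 6 months before enrolment is an exclusion criterion, the device is unblinded (Comparison to Previous Work), and the first sensor is placed at Visit 1. One sensor at Visit 1 plus five given at Visit 2 makes six over 12 weeks, or 12/6 = 2 weeks each. The earliest window is therefore about weeks 0-2 of unblinded wear, after education has begun.

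Assume a 15-point gain in time in range, a share s of it reached linearly over weeks 0-2, the rest afterwards, and the full gain present in the final window. A baseline averaged over weeks 0-2 already holds s/2 of the gain:

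- s = 30%: 15 × (1 − 0.15) = 12.75 points.
- s = 50%: 15 × (1 − 0.25) = 11.25 points.

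The contrast would read about 11.3 to 12.8 in place of 15.

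**The case against.** **The survey cannot precede CGM, and the protocol is open about its baseline.** Both are true. The article marks the second visit as the survey baseline each time, so this is not a contradiction. Disclosure does not make the contrast fit items that are already change reports.

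**Behaviour change is measured properly elsewhere.** The SDSCA is given at Visit 1 and week 12 and covers diet and exercise. This limits the damage. It does not alter the separate hypothesis tied to the survey from the second visit.

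**Descriptive percentages would reveal the pattern.** Statistical Analyses plans percentages for categorical variables, the survey is given at four visits, and open-ended questions ask what changed. A reader might infer that the study would conclude nobody changed when everybody had. That goes too far, because percentages at Visits 2 and 5 would show Yes at both. What stands is that the contrast named for the hypothesis would show no difference in that case.

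**Not every item is a change score.** Eight of the ten closed items mention the time since using or wearing CGM, so a reader might infer that the whole instrument is affected. It is not. Scan frequency, motivation, medication-taking and activity on a glucose rise record a level, and Visit 2 to Visit 5 change in them is meaningful. The carbohydrate item can also show a later move from reducing to avoiding.

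**The sensor point is inference.** The article defines no baseline window, and a fuller document may. A reader might infer a week-2 to week-12 contrast that loses the whole early gain, taking the assumed 15 points down to 15 × 0.7 = 10.5 or 15 × 0.5 = 7.5. That requires a baseline at the end of week 2, which the article states for the survey only. What survives under any window is that it falls after the intervention began.

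**Conclusion.** The point holds for four survey items and arguably for two more. For these, the stated contrast measures only change that first appears after week 2, while the intervention begins at week 0. With 12 of 20 reporting a change at week 12 and half of them early, the contrast shows 30 points against 60% reporting the change. These inputs are assumed; the direction follows from the schedule and the wording. The 60% is self-reported change without a comparator, not an estimate of the effect of CGM.

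The sensor-metric part is secondary and rests on the schedule. Early change is diluted, not wholly lost, if weeks 0-2 are averaged. The outcomes counting participants who gain 5% or 10% or more in time in range would share the shifted reference.

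The primary HbA1c outcome, the two HbA1c-threshold outcomes in Textbox 2 and the SDSCA have Visit 1 measurements and are unaffected. This is a worthwhile correction to secondary outcomes and no threat to the main comparison.

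**What to change.** 1. For sugared beverages, high-carbohydrate foods, nutrition labels and physical activity, make the outcome the proportion reporting the change at week 12, and at each visit, with exact confidence intervals. Take as denominator the participants able to change, and report separately the number who chose an option describing their habits before CGM. Treat noticing food effects and healthier lifestyle in the same way, with all respondents as denominator.
2. For these items, use Visit 2 to Visit 5 only to describe persistence or later change.
3. Keep the Visit 2 to Visit 5 comparison for scan frequency, motivation, medication-taking and activity on a glucose rise. In the medication item, count the answer about adherence before CGM separately, because it has no place on the ordered scale.
4. Reword the survey hypothesis to match.
5. Name the sensor-metric reference window, call it early CGM wear after education has begun, and do not interpret the result as change from before the intervention.

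The cost is outcome and analysis wording. Forms, sensors and visits stay the same, and only 3 participants had been enrolled when the article was written.
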